## Abstract

**Background:**

Complaints of imbalance are common non-resolving signs in individuals with post-concussive syndrome. Yet, there is no consensus rehabilitation for non-resolving balance complaints following mild traumatic brain injury (mTBI). The heterogeneity of balance deficits and varied rates of recovery suggest varied etiologies and a need for interventions that address the underlying causes of poor balance function. Our central hypothesis is that most chronic balance deficits after mTBI result from impairments in central sensorimotor integration that may be helped by rehabilitation. Two studies are described to 1) characterize balance deficits in people with mTBI who have chronic, non-resolving balance deficits compared to healthy control subjects, and 2) determine the efficacy of an augmented vestibular rehabilitation program using auditory biofeedback to improve central sensorimotor integration, static and dynamic balance, and functional activity in patients with chronic mTBI.

**Methods:**

Two studies are described. Study 1 is a cross-sectional study to take place jointly at Oregon Health and Science University and the VA Portland Health Care System. The study participants will be individuals with non-resolving complaints of balance following mTBI and age- and gender-matched controls who meet all inclusion criteria. The primary outcome will be measures of central sensorimotor integration derived from a novel central sensorimotor integration test. Study 2 is a randomized controlled intervention to take place at Oregon Health & Science University. In this study, participants from Study 1 with mTBI and abnormal central sensorimotor integration will be randomized into two rehabilitation interventions. The interventions will be 6 weeks of vestibular rehabilitation 1) with or 2) without the use of an auditory biofeedback device. The primary outcome measure is the daily activity of the participants measured using an inertial sensor.

**Discussion:**

The results of these two studies will improve our understanding of the nature of balance deficits in people with mTBI by providing quantitative metrics of central sensorimotor integration, balance, and vestibular and ocular motor function. Study 2 will examine the potential for augmented rehabilitation interventions to improve central sensorimotor integration.

**Trial registration:**

This trial is registered at clinicaltrials.gov (NCT02748109)

## Background

Between 1.6 and 3.8 million sports-related mild traumatic brain injuries (mTBI) occur annually in the United States [1] and up to 15% of military combat veterans sustain mTBI [2]. The estimated annual cost of TBI, including lost productivity, exceeds $60 billion [3]. While self-reported symptoms of mTBI typically recover within three months [4], between 11 and 64% of individuals, depending on diagnostic criteria, develop post-concussive syndrome with persistent, non-resolving symptoms [5]. Despite the high incidence and cost to society, studies investigating the treatment of chronic mTBI symptoms have been scarce. In particular, complaints of imbalance are common following mTBI [6, 7] and are significant contributors to anxiety and difficulty returning to work [8]. Yet, there is currently no consensus, evidence-based rehabilitation procedure for balance complaints following mTBI [9].

The difficulty establishing consensus rehabilitation protocols is likely due to the complex nature of balance deficits in individuals with mTBI that can include neurological damage to the brainstem [10, 11], thalamus [12], and cerebellum [13], and / or injury to peripheral vestibular organs [14–17]. Sensory information from the vestibular, visual, and somatosensory systems are integrated in the central nervous system to control static and dynamic balance (Fig. 1). In patients with mTBI, vestibular function can be impaired by damage to the peripheral vestibular organs. The semicircular canals can be impaired in up to two-thirds of individuals with mTBI [15, 17], and the otolith organs are also susceptible to damage from mTBI [14, 16]. In addition to disrupting vestibular function, mTBI has also been linked with central deficits affecting ocular motor function including extended saccadic latency [18] and poor visual tracking accuracy during smooth pursuit tasks [19, 20]. In one study, 60% of individuals with mTBI had errors during pursuit whereas no controls exhibited similar errors [21].

**Fig. 1 Fig1:**
[figure not shown]
Sensory systems contributing to static and dynamic balance

A proportion of individuals with mTBI who do not have prominent or measurable sensory deficits may still have balance problems attributable to abnormal central control of balance. Central sensorimotor integration is a critical aspect of balance control that may underlie dysfunction in static and dynamic balance. Proper central sensorimotor integration relies on the central nervous system to 1) select the optimal combination of sensory sources for balance and 2) reweight the sensory contributions as sensory conditions change [22, 23]. When peripheral vestibular, visual, and somatosensory systems are intact, difficulty performing static or dynamic balance tasks under challenging surface and/or visual conditions may be due to centrally-mediated suboptimal weighting and/or reweighting of vestibular, visual, and somatosensory information or due to abnormal sensory-to-motor transformations that inappropriately scale the magnitude of corrective motor actions [22–24]. For example, standing or walking on compliant foam or irregular surfaces requires the nervous system to rely more on vestibular and visual inputs while down-weighting the normal dependence on somatosensory information [22]. This reweighting is also important for individuals with sensory impairment, as altered patterns of weighting are necessary to compensate for the sensory dysfunction. Some patterns of compensation may be more functional than others, suggesting an important role of rehabilitation in helping subjects develop effective compensation strategies to improve recovery of central sensorimotor integration and balance [24]. However, central sensorimotor integration has not been systematically characterized in patients with mTBI, regardless of sensory loss.

The lack of knowledge about central sensorimotor integration following mTBI may be in part due to the current clinical tools used to assess balance, gait, and sensorimotor integration. The Balance Error Scoring System (BESS) is the most frequently administered clinical balance assessment for patients with suspected mTBI. Yet, the BESS suffers from a high degree of subjectivity, provides only limited, low-resolution information about the balance control system [25], and is not sensitive beyond the acute stages of mTBI [26]. Balance measures using force platforms and sophisticated post-processing and analysis techniques have shown greater sensitivity in detecting long-lasting postural deficits [27–31]. Similar to static balance, measures of dynamic balance, such as trunk motion during gait [32–35] have shown persistent impairment post-concussion. Sensitive, objective measures of balance can be obtained using wearable sensors [36–39] and are well-suited for clinical and rehabilitation environments [40, 41].

For instance, wearable sensors enable biofeedback based on quantitative measurements of balance and gait. Specifically, auditory biofeedback (ABF), which communicates sway through changes in the pitch or location of a tone, has shown promise in aiding balance and retraining central sensory integration mechanisms in populations with balance impairments [42, 43]. Quantitative measures of sway and body position are communicated to the patient via audition, in real-time, to augment existing sensory information and provide accurate information to the central nervous system about body sway that may help recalibrate distorted sensory integration. Compared to visual biofeedback paradigms, ABF is particularly well suited for populations with mTBI as the auditory cue does not interfere with other postural sensory systems, such as vision.

The heterogeneity of balance deficits and varied rates of recovery after mTBI suggest varied etiologies and a need for interventions that address the underlying causes of poor balance function. Over-simplified clinical balance measures often do not account for the complex integration of sensory and motor systems. Therefore, the first goal of this study is to characterize balance deficits in people with mTBI who have chronic, non-resolving balance deficits compared to healthy control subjects without a history of mTBI. We hypothesize that a) objective measures of central sensorimotor integration, static and dynamic balance will better distinguish people with mTBI from control subjects than clinical measures, b) a subset of people with mTBI will have abnormal central sensorimotor integration test measures, even without peripheral vestibular or ocular motor deficits, and c) the relationship between poorer static/dynamic balance performance and mTBI is regulated/mediated by central sensorimotor integration. The second goal is to determine if augmenting a traditional balance rehabilitation program with a wearable-sensor based ABF system improves central sensory integration in patients with chronic mTBI compared to the standard balance rehabilitation program. Our central hypothesis is that chronic balance deficits after mTBI result from impairments in central sensorimotor integration that may be helped by rehabilitation that challenges balance while simultaneously providing feedback on balance performance. We hypothesize that a) central sensorimotor integration scores will improve with rehabilitation and ABF will increase the improvement of central sensorimotor integration scores beyond the standard of care, b) intervention with ABF will improve objective measures of balance and c) people with central sensorimotor integration impairment will show sustained improvement in central sensorimotor integration scores and balance after rehabilitation with ABF.

## Methods / Design

This study has two parts: Study 1) A cross-sectional study to identify and characterize balance control strategies after mTBI compared to healthy controls, and Study 2) An interventional randomized pilot study using a novel ABF rehabilitation technique to improve central sensorimotor integration after mTBI. All subjects will complete baseline clinical sensory, ocular motor, vestibular, neurocognitive, static and dynamic balance, and central sensorimotor integration testing. Following baseline testing, a subset of mTBI participants will be randomized into two treatment groups for 6 weeks of rehabilitation. Within 1 week after completing the rehabilitation program, subjects will repeat the balance and central sensorimotor integration testing to examine the short-term effects of rehabilitation. Subjects will complete the balance and central sensorimotor integration testing a third time, 6 weeks after completion of the rehabilitation, to assess retention. This trial is registered at clinicaltrials.gov (NCT02748109).

### Participants

The study will include 65 mTBI participants and 65 control subjects for the cross-sectional arm of the study. All subjects will be between the ages of 18 and 60. Participants in the mTBI group will have a diagnosed mTBI or concussion and chronic, non-resolving complaints of balance problems determined by a score >0 on the Dizziness Handicap Inventory (DHI) at the time of testing and > 3 months post-injury. Control subjects will be gender and age matched to the mTBI group. For the second arm of the study, a subset of 40 mTBI subjects with abnormal central sensorimotor integration with or without peripheral vestibular or ocular motor deficits will be randomized into two rehabilitation groups, experimental treatment and standard of care, consisting of two rehabilitation sessions per week for 6 weeks. All subjects will be tested at either Oregon Health & Science University or the VA Portland Health Care System. All rehabilitation will take place at Oregon Health & Science University. Informed written consent will be obtained from all participants.

### Inclusion and exclusion criteria

Inclusion criteria for mTBI recruitment are 1) a diagnosis of mTBI based upon VHA/DoD criteria with persisting symptoms >3 months post injury [44], 2) between 21–50 years old, 3) a score >0 on the DHI, 4) minimal cognitive impairment; a score between 0 and 8 on the Short Blessed test for cognitive function [45], and 5) may or may not have had a loss of consciousness (LOC) with their initial injury. Inclusion criteria for controls are between 21–50 years old and no history of mTBI or brain injury. Exclusion criteria are: 1) have had or currently have any other injury, medical, substance or neurological illness that could potentially explain balance deficits (e.g., CNS disease, stroke, moderate TBI, lower extremity amputation) 2) meet criteria for moderate to severe substance use disorder within the past month, as defined by DSM-V, 3) display behavior that would significantly interfere with validity of data collection or safety during study, 4) be in significant pain during the evaluation (5/10 by patient subjective report), 5) be a pregnant female (balance considerations), 6) have past history of peripheral vestibular pathology or ocular motor deficits, 7) have significant hearing loss that would interfere with Study 1 no worse than 60 dB HL (PTA 0.5–3 kHz) and Study 2; hearing loss no worse than 30 dB HL (PTA 0.5–3 kHz), in better ear, with the difference in ears being less than 15 dB PTA, or 8) be unable to abstain for 24 h in advance of testing in the use medications that might impair their balance.

### Study 1: Characterization of balance deficits

#### Assessment procedures

All people who are eligible per phone screening will come into the clinic for the informed consent process. An investigator will verbally explain the consent form, allow the person ample time to read through the consent form and then will acknowledge consent by signing the form. All subjects will first read and sign consent forms. For study 1, 65 mTBI participants and 65 control subjects will be assessed on a battery of tests designed to measure vestibular function, sensorimotor integration, static and dynamic balance, cognition, reaction time, clinical sensory loss, and self-reported symptoms. All protocols have been approved by the OHSU Institutional Review Board.

Participants will complete a novel central sensorimotor integration test (CSMI test) [22] on a modified research NeuroCom platform using custom-designed, low-amplitude (2° and 4° peak-to-peak) pseudorandom stimuli that apply continuously repeated cycles of wide bandwidth surface-tilt and/or visual-tilt stimuli with individual tests lasting ~5 min. The participants’ anteroposterior (AP) body displacement at shoulder and hip levels, and surface and visual surround rotation angles will be recorded. Subjects will perform 8 trials (2 amplitudes x 4 test conditions) in one session with trials presented in a randomized order and interspersed with rest breaks (Table 1). Anthropometric measures will be obtained for the purpose of estimating body mechanics needed for later analysis (moment of inertia, mass, height of center of mass, CoM) [22].

**Table 1 Tab1:** Aim 1 CSMI test conditions and sensory weight comparisons

Condition	Vision	Support Surface	Visual Surround	Sensory Weight Comparisons
1	EC	PRS	--	*W* _*prop*_ vs. *W* _*vest*_
2	EO	PRS	Fixed	*W* _*prop*_ vs. *W* _*vis*_ *+ W* _*vest*_
3	EO	Fixed	PRS	*W* _*vis*_ vs. *W* _*prop*_ *+ W* _*vest*_
4	EO	PRS	PRS	*W* _*prop*_ *+ W* _*vis*_ vs. *W* _*vest*_

*EC* eyes closed, *EO* eyes open, *PRS* pseudorandom stimulus

#### Primary outcome measure

The primary outcome measures of central sensorimotor integration are the parameters derived from a model-based interpretation of CoM sway evoked by pseudorandom stimuli (Table 2). The procedure for calculating these parameters is to (1) calculate CoM angular displacement from experimental measures of hip and shoulder displacement on each test trial, (2) use Fourier methods to calculate a frequency response function, FRF (e.g. Fig. 2d) [46], and (3) adjust parameters of a model of the balance control system represented by the Fig. 2a block diagram using a constrained optimization algorithm (Matlab “fmincon” function; The Mathworks, Inc., Natick, MA) until the model-derived FRF optimally matches the experimental FRF (e.g. model-derived FRFs in Fig. 2d) [22, 47]. This analysis procedure will be applied to each of the 8 individual tests performed by each subject. The full set of model parameters are defined in Table 2.

**Table 2 Tab2:** Balance control model parameters

*W* _*vis*_ *, W* _*prop*_ *, W* _*vest*_	Sensory weights of visual, proprioceptive, and vestibular contributions
*K* _*p*_ *, K* _*d*_	Neural controller parameters (sensory-to-motor transform)
*K* _*t,*_	Gain constant (torque feedback pathway)
*t* _*d*_	Net feedback time delay

**Fig. 2 Fig2:**
[figure not shown]
CSMI methods with example data and analysis. (**a**) A feedback control model forms the basis for identifying model parameters (Table 2) that account for experimentally evoked body-in-space (BS) sway, representing angular tilt of the body center-of-mass (CoM), evoked by support surface (SS) and/or visual surround (VS) rotations. (**b**) An example of one cycle of a pseudorandom surface-tilt stimulus that evoked the CoM body sway (averaged across 5 stimulus cycles) shown in (**c**) for a Control subject and TBI subject. (**d**) Frequency domain analysis of stimulus/response data in (**b**) and (**c**) yields frequency response functions (FRFs) expressed as gain (ratio of CoM response amplitude to stimulus amplitude) and phase (timing of response relative to stimulus) measures as a function of frequency components in the pseudorandom stimulus. Parameters of the model in (**a**) are calculated by a fit procedure that finds parameters that optimally account for the FRF gain and phase data

The parameters include sensory weights that represent the relative contributions of proprioceptive, visual, and vestibular sensory information to balance control such that in each of the 4 test conditions the sum of weights equals 1. These weights are known to vary with test conditions that alter the availability (e.g. eyes open or closed) or reliability (e.g. varying stimulus amplitudes) of sensory information and are affected by sensory abnormalities (22, 24). For condition 1 tests (surface tilt stimulus with eyes closed) the model fit to the experimental FRF provides a measure of the proprioceptive contribution (Wprop). With eyes closed, the visual contribution (Wvis) is zero and therefore the vestibular contribution is Wvest = 1 – Wprop. Condition 2 tests also use a surface tilt stimulus but eyes are open with both visual and vestibular cues providing accurate orientation information. The model fit again provides an estimate of Wprop but now 1 – Wprop = Wvis + Wvest. Condition 3 tests present a visual tilt stimulus where the model fit provides a measure of Wvis and 1 – Wvis = Wprop + Wvest. Finally condition 4 tests simultaneously present the same surface and visual-tilt stimulus. In this condition the model fit provides a measure of Wprop + Wvis with Wvest = 1 – (Wprop + Wvis).

The neural controller parameters Kp and Kd (Table 2) represent the transformation from an internal sensory error signal (i.e. deviation from a desired body orientation) to a corrective ankle torque the moves the body toward a body orientation that reduces the sensory error. The neural controller parameters (Kp and Kd) are known to scale with subject anthropometrics [22] and, therefore, will be normalized prior to performing across subject comparisons. The balance model also assumes that a sense of effort contributes to the sensory error signal. This effort sense is represented by a torque feedback pathway with parameter Kt that is a scaling factor applied to the mathematical integration of the corrective ankle torque signal. This feedback pathway accounts for the low frequency characteristics of the FRFs that show gain declines and phase advances at frequencies below about 0.1 Hz (Fig. 2d). The time delay parameter td represents all delays in the system including sensory transduction, neural transmission, central processing, and muscle activation. The time delay parameter accounts for a substantial portion of the increasing FRF phase lag with increasing frequency.

#### Sample size

Power analysis for Study 1 was derived from a pilot dataset of 12 control subjects who participated in CSMI tests with the goal of estimating the sample size necessary for a normative reference group. This was defined as the number of control subjects necessary to see a coefficient of variation (CV) of less than 10%, a common threshold for measurement precision, in the CMSI outcome measures in order to develop a robust reference control group with a reasonable and acceptable amount of variability (49). Estimation was done with bootstrapping techniques using the stiffness control parameter (Kp) of the CMSI test of the pilot cohort as a sample distribution. For a considered sample size (ranging from 10 to 100 subjects), 1000 random samples with replacement were taken from the cohort’s Kp dataset to simulate a null distribution at that sample size and estimate the corresponding CV. Based on these permuted samples, the CV of the Kp parameter is expected to be less than 10% with 65 subjects, giving an adequately representative reference group. This same sample size of 65 will allow for a CV of ~6.5% in other CSMI measures such as visual sensory weighting. Therefore, a cohort of 65 mTBI subjects should be more than sufficient to properly identify any underlying classification differences arising from central sensorimotor integration abnormalities.

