#### Statistical analysis

To determine if objective/novel measures of balance will better distinguish people with mTBI from control subjects than clinical measures, we will use logistic regression classification models. Improvements in classification will be determined by calculating the area under the curve (AUC) of the receiver-operator characteristic and then comparing AUC for each traditional clinical measure with the novel objective measures. Significance will be assessed using bootstrapping to determine if the observed differences in AUC are greater than would be expected by chance at a level of 0.05.

To determine if a subset of people with mTBI will have abnormal CSMI test measures, even without peripheral vestibular or ocular motor deficits, we will use descriptive statistics to characterize the distribution of CSMI test measures and vestibular/ocular motor scores. We will define CSMI test measures and vestibular/ocular motor scores as abnormal if the scores are greater than 2 standard deviations from the mean in controls. We will then classify mTBI subjects into one of 4 CSMI-vestibular/ocular motor categories 1) abnormal CSMI –abnormal vestibular/ocular motor scores, 2) abnormal CSMI –normal vestibular/ocular motor scores, 3) normal CSMI –abnormal vestibular/ocular motor scores, 4) normal CSMI –normal vestibular/ocular motor scores.

To determine if the observed relationship between poorer static/dynamic balance performance and mTBI is regulated/mediated by central sensorimotor integration, we will use mediation analysis. Mediation analysis [49] will allow for the partitioning of the association between mTBI and chronic imbalance into two parts, the direct relationship of mTBI on balance impairment as well as the causally mediated effect of mTBI on central sensorimotor integration, which, in turn is having the actual effect on imbalance. These varying generative mechanisms of balance deficits will be assessed by utilizing linear models relating mTBI to CSMI test measures alongside models of mTBI and CSMI test measures jointly affecting imbalance using the apportionment methods described by Baron and Kenny [49].

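### Study 1's 65 per group is a control-group precision target; it does not support the claim that 65 mTBI subjects suffice for any classification difference

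*Protocol article*

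**What the plan says.** The sample size section of Study 1 calls its calculation a power analysis. The data are "derived from a pilot dataset of 12 control subjects who participated in CSMI tests", and the work is done "with the goal of estimating the sample size necessary for a normative reference group". For sample sizes from 10 to 100, "1000 random samples with replacement were taken from the cohort’s Kp dataset to simulate a null distribution at that sample size", and a CV is estimated at each size. Two results are reported. For Kp, "the CV of the Kp parameter is expected to be less than 10% with 65 subjects, giving an adequately representative reference group". For the rest, "This same sample size of 65 will allow for a CV of ~6.5% in other CSMI measures such as visual sensory weighting". The section ends by concluding from this that "a cohort of 65 mTBI subjects should be more than sufficient to properly identify any underlying classification differences".

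The statistical analysis section of Study 1 sets out what the 65 and 65 are used for:

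- **AUC comparison.** Hypothesis (a) is tested by "comparing AUC for each traditional clinical measure with the novel objective measures", with bootstrap significance at the 0.05 level.
- **Classification.** mTBI subjects are placed descriptively in four categories, using a cut-off of 2 SD from the control mean.
- **Mediation.** A mediation analysis relates mTBI, CSMI measures and balance.

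**The concern.** There are two faults.

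1. **The CV is not defined.** It could be the CV of the sample mean, the CV of the estimated SD, or the between-person spread (SD divided by mean). The first two fall as the sample grows. The third does not, so it could not select a sample size. A reader cannot tell what 65 controls are precise for.

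2. **The conclusion does not follow from the premises.** Everything before the last sentence concerns controls only. The only mTBI pilot data in the article (3 subjects, Study 2 sample size section) are used to size Study 2. A statement about controls' Kp says nothing about how well 65 mTBI subjects can be told apart from 65 controls, or about how large a difference between two AUCs can be detected.

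At stake is how Study 1's first hypothesis is read. The Discussion ties a conclusion about the need for objective measurement to a significantly greater AUC. A reader who accepts the sufficiency sentence will credit the study with more sensitivity than the design is shown to have.

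**Working it through.** **Inputs from the protocol article.** 65 mTBI and 65 controls (Participants); CV below 10% for Kp and about 6.5% for other CSMI measures at n = 65 (Study 1, Sample size); AUC differences tested at 0.05 and the 2 SD rule (Study 1, Statistical analysis).

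**Assumed, because the article gives no value.** Two-sided test; clinical AUC 0.70; correlation r between the two AUC estimates from 0 to 0.6; normality for the cut-off calculation.

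**Step 1. Can the plan's 65 be reproduced?** No: the mean and SD of the pilot Kp values are not given. The three readings give the following.

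- *CV of the mean* = between-person CV / √n. At n = 65, 10% corresponds to a between-person CV of 0.10 × √65 = 0.806. This is an upper bound, since the text says less than 10%. The 6.5% corresponds to 0.065 × √65 = 0.524.
- *CV of the SD*, normal data = 1/√(2(n − 1)). At n = 65 this is 1/√128 = 8.8%; it equals 10% at n = 51. The plan, however, bootstraps 12 observed values, and then the approximation is √((kurtosis − 1)/(4n)). At n = 65, 10% needs a kurtosis of 1 + 4 × 65 × 0.01 = 3.6, and 6.5% needs 1 + 4 × 65 × 0.004225 = 2.1. Bootstrapping simulated sets of 12 normal values gave a CV of the SD at n = 65 of roughly 5% to 11% in most sets. Both published figures are therefore attainable on this reading.
- *Between-person spread.* In a bootstrap from an assumed 12-value set with CV about 0.3, SD/mean averaged 0.275 at n = 10 and 0.279 at n = 65. It does not shrink, so it cannot lead to 65.

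None of the three readings contains mTBI data, an AUC, a significance level or a power.

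**Step 2. What 65 versus 65 delivers for the AUC comparison.** The Hanley–McNeil variance with n per group is

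Var(A) = [A(1 − A) + (n − 1)(Q₁ − A²) + (n − 1)(Q₂ − A²)] / n², where Q₁ = A/(2 − A) and Q₂ = 2A²/(1 + A).

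For A = 0.70: Q₁ = 0.538, Q₂ = 0.576, Var = 0.00209, SE = 0.046. For A = 0.80: Q₁ = 0.667, Q₂ = 0.711, Var = 0.00152, SE = 0.039.

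The SE of the difference is √(Var₁ + Var₂ − 2r × SE₁ × SE₂), and power = Φ(gain/SE − 1.96).

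Worked case, 0.70 versus 0.80 with r = 0: SE = √(0.00209 + 0.00152) = 0.060; power = Φ(0.10/0.060 − 1.96) = 38%.

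| Assumed r | Power, gain 0.05 | Power, gain 0.10 | Power, gain 0.15 | Gain detectable at 80% power |
|---|---|---|---|---|
| 0 | 12% | 38% | 75% | 0.16 |
| 0.2 | 14% | 46% | 83% | 0.145 |
| 0.4 | 18% | 57% | 92% | 0.13 |
| 0.6 | 24% | 74% | 98% | 0.11 |

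**Step 3. Precision of the 2 SD cut-off.** Under normality, the SE of mean + 2 SD in SD units is √(1/65 + 4/(2 × 64)) = √(0.0154 + 0.0313) = 0.216. The estimated limit can then lie between 2 − 1.96 × 0.216 = 1.58 and 2 + 1.96 × 0.216 = 2.42 SD. A nominal upper tail of 2.3% may in truth be anything from about 5.7% to 0.8%.

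**The case against.** The best defence is that the section states its goal as a normative reference group, and that a precision target is a sensible way to size one. If the CV of the SD is meant, it bears directly on the 2 SD rule: of the 0.216 SD standard error in step 3, the SD component alone is 2 × 8.8% = 0.177 SD. The wording about resampling at each sample size also fits the CV of a sampling distribution, which does fall with n. All of this stands, and it is why the 65 should be kept.

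Several stronger readings are tempting, but the documents do not support them.

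- *The right answer was 51, not 65.* That holds only for normal data; the plan resampled 12 observed values, and step 1 shows that 10% and 6.5% are both attainable.
- *The 2 SD rule could never flag a low Kp or a low visual weight.* This takes the CV-of-the-mean reading as established and the 10% bound as an equality. For the visual weight it turns on rounding: a CV of 6.2% instead of about 6.5% gives a between-person CV of 50%, which puts mean − 2 SD at zero. The article also normalizes Kp before subjects are compared and does not say whether the pilot Kp was normalized.
- *The CV cannot inform classification at all.* On the SD reading it does.
- *A non-significant AUC difference will be read as equivalence.* No sentence says so; the Discussion covers only a significantly greater AUC.
- *65 is too few.* Power is 75% to 98% for a gain of 0.15, and a plain two-group mean comparison has 81% power at d = 0.5.

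One may also say that AUC power can be left to the full protocol or the analysis plan. That is so, and its absence is not the point. The point is that the article states a sufficiency conclusion and rests it on a calculation that cannot carry it.

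**Conclusion.** The sufficiency sentence is wrong as written. It draws a conclusion about mTBI subjects and discrimination from the precision of a control-group parameter, and the AUC comparison at 65 versus 65 cannot be relied on to find any difference. Under the stated assumptions (clinical AUC 0.70, correlation 0 to 0.6, two-sided 0.05), the gain detectable with 80% power is about 0.11 to 0.16. Power is 38% to 74% for a gain of 0.10 and 12% to 24% for a gain of 0.05. These figures rest on assumed AUCs and correlations, but the conclusion that not every difference is detectable holds across the whole range. The choice of 65 itself is neither confirmed nor refuted, and no arithmetic error in the CV figures is shown; the quantity they describe is simply not named.

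**What to change.** In the Study 1 sample size section:

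1. Keep 65 per group, and describe it as a precision target for the control reference group, not as a power analysis.
2. Say which CV is meant: of the mean, of the SD, or of another summary.
3. Delete the sentence that 65 mTBI subjects are more than enough for any classification difference.
4. Put in its place the AUC difference detectable at 65 versus 65. An example is about 0.11 to 0.16 with 80% power, labelled as assuming a clinical AUC of 0.70, a correlation of 0 to 0.6 and two-sided 0.05. The investigators should substitute their own expected values where they have them.
5. Add the precision of the 2 SD cut-off: standard error about 0.22 SD with 65 controls under normality.

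The cost is a weaker sufficiency claim. No participants are added and no analysis changes.
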